### Concomitant medication

Cannabis or cannabinoid-based medications (up to and including within 30 days of randomisation) are prohibited during the trial. Live vaccines should be avoided during and for six weeks after completion of chemotherapy. Patients are permitted to receive COVID-19 vaccines whilst on trial treatment.

Patients with genetic glucuronidation disorders (e.g., Gilbert’s disease) must be treated with caution when nabiximols is co-administered.

A review of patients’ dosing regimen is advised when co-administering nabiximols with CYP3A4 substrates and other drugs metabolised through cytochrome P-450 enzymes e.g., coumarins, statins, beta-blockers, and corticosteroids.

Concomitant treatment of nabiximols with strong enzyme inducers (e.g., rifampicin, carbamazepine, phenytoin, phenobarbital, St John’s Wort) should be avoided whenever possible.

Due to possible adverse interactions with nabiximols, sedatives, muscle relaxers, anti-spasticity agents, and alcohol these should be avoided.

### Outcome measures

The primary outcome is OS defined as the time in whole days from the date of randomisation to the date of death from any cause. Patients who are alive at the time of analysis will be censored at the date last seen alive. Secondary outcome measures are overall survival at 12 months (OS12) (of particular clinical relevance is the overall survival at 12 months from the date of randomisation with overall survival at six months and 24 months also of interest); PFS, defined as the time in whole days from date of randomisation to the date of the first documented evidence of disease progression or death (from any cause); and HRQoL assessed at screening, and then every eight weeks until the end of treatment. HRQoL will be assessed with the EORTC QLQ-C30 [19, 20], EORTC BN20 [21, 22], single items from the EORTC item library, and the EQ-5D-5L [23].

### Statistical analysis plan

#### Sample size

The target sample size is 234 patients based on testing the null hypothesis of no difference between the treatment arms in terms of OS, i.e., a hazard ratio (HR) = 1 and assumes exponential distribution for survival times. Calculations assume a recruitment period of 18 months and follow-up period of 12 months. As a phase II trial, the design uses a relaxed one-sided significance level of 10% (i.e., α = 0.1) and a randomisation ratio of 2:1 in favour of the experimental treatment arm. The expected median survival time on the placebo arm is 12 months, which equates to a hazard rate of 0.058 [6, 24]. Given these design parameters, the trial requires 132 events to have 80% power (i.e., β = 0.2) to detect a difference with a hazard ratio of 0.68, i.e., median survival time of 17.6 months on the experimental treatment arm and hazard rate of 0.039. Given the results from the phase I trial [16], we believe this is a plausible benefit to target. It is estimated that we need to recruit 222 patients during the 18-month recruitment period to observe this number of events; a further 5% to cover potential dropouts has been added to give a target sample size of 234. The trial includes an initial feasibility study that, based on a pragmatic rationale, will incorporate the first 40 patients recruited.

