## Methods

### Trial design

ARISTOCRAT is a phase II, multi-centre, double-blind, placebo-controlled, randomised trial to compare nabiximols with placebo in patients with recurrent MGMT methylated GBM suitable for treatment with TMZ. The trial has a target sample size of 234 patients who will be randomised on a 2:1 basis to receive either nabiximols or placebo, respectively, in combination with standard TMZ treatment (Fig. 1). The trial includes an initial feasibility study of 40 patients to confirm safety, compliance, and achievability of planned target recruitment. There are no formal criteria for evaluating feasibility but once 40 patients have been recruited, the independent Data Monitoring Committee (DMC) will review AE data, details on protocol treatment received, monthly recruitment rates and projected recruitment to make recommendations on trial continuation.

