### Patient recruitment

This trial aims to recruit patients at UK participating centres following referral from their local multidisciplinary team at point of recurrence, including confirmation of radiological recurrence from a consultant neuro-radiologist. Recruitment will be over three years, with participants followed up for at least one year from the start of treatment or until death. Key eligibility criteria are listed in Table 1.

**Table 1 Tab1:** Key eligibility criteria for ARISTOCRAT

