#### Outcome analyses

Overall survival time will be analysed using the Kaplan-Meier method to estimate and plot the survivor functions for each treatment arm, together with summary statistics of median and 12-month survival rates. In addition, 6-month and where available 24-month survival rates will be reported. The difference between treatment arms will be estimated using a hazard ratio generated from a Cox regression model. All estimates will be reported with one-sided 90% confidence intervals. The null hypothesis of no difference between the treatment arms in terms of overall survival time will be tested using the Cox regression model. The primary analysis will be on all patients who have received at least two cycles of protocol treatment.

Progression-free survival time will be analysed in the same way as OS. Measures of HRQoL will be reported on each treatment arm as means over time with 95% confidence intervals. The incidence of adverse events will be reported in the case report form (CRF) and patient diaries on each arm and compared descriptively.

Final analysis of the completed phase II trial will occur once all participants have been recruited and followed up for at least 12 months from closure of the trial to recruitment.

The treatment effect will be evaluated for subgroups of patients defined by age (≤ 70 vs. > 70 years), performance status (Karnofsky Performance Status 60–79 vs. 80–100), sex (male vs. female), symptomatic vs. asymptomatic at baseline, numbers of sprays per day and re-resection group.

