### Trial status

Recruitment for the trial opened on 03-Feb-2023 and is expected to last three years.

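### The sample size is worked out for 18 months of recruitment, but the trial recruits for three years, so the stated link from patients to events does not describe it

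*Protocol article*

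**What the plan says.** All places are in the protocol article.

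- **Sample size:** "Calculations assume a recruitment period of 18 months and follow-up period of 12 months". On that basis 132 events are required for 80% power at a hazard ratio of 0.68, one-sided 10% level. To observe them, 222 patients are to be recruited within the 18 months, and 5% for dropout brings the target to 234.
- **Patient recruitment:** "Recruitment will be over three years".
- **Trial status:** "Recruitment for the trial opened on 03-Feb-2023 and is expected to last three years".
- **Outcome analyses:** "Final analysis of the completed phase II trial will occur once all participants have been recruited and followed up for at least 12 months", counted from closure of recruitment. The 132 events are not mentioned there. The same section limits the primary analysis to patients who received at least two cycles of protocol treatment.

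**The concern.** The two recruitment periods differ by a factor of two. In a survival trial the recruitment period is a working input: together with the follow-up period it fixes the fraction of patients expected to have died by the analysis, and so the number of patients needed for a given number of events. If recruitment takes three years and the analysis waits a further 12 months, early recruits are followed for up to 48 months instead of 30, and more deaths accrue from the same patients.

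At stake is whether the stated patient number, expected events, power and analysis timing describe the trial being run. The final analysis is placed by calendar, with no stated tie to the 132 events, so a change in the accrual period passes straight through to the information available at that analysis.

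**Working it through.** **Inputs, all from Sample size unless noted.** Exponential survival. "The expected median survival time on the placebo arm is 12 months, which equates to a hazard rate of 0.058"; unrounded, λc = ln 2 / 12 = 0.05776. Hazard ratio 0.68, so λe = 0.68 × 0.05776 = 0.03928. One-sided α = 0.10 (z = 1.2816). "a randomisation ratio of 2:1 in favour of the experimental treatment arm". Recruitment R = 18 months there, against R = 36 in Patient recruitment and Trial status. F = 12 months after recruitment closes. Uniform accrual is my assumption; the article states no pattern.

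**Formulae.**
- P(event) = 1 − [exp(−λF) − exp(−λ(F + R))] / (λR), weighted 1/3 placebo and 2/3 experimental.
- Power with d events (Schoenfeld, 2:1) = Φ(√(d × 2/9) × |ln 0.68| − 1.2816), with |ln 0.68| = 0.3857.

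**Step 1: reproduce the plan's figures (R = 18, F = 12).**
- Placebo: 1 − (0.5000 − 0.1768)/1.0397 = 0.689.
- Experimental: 1 − (0.6242 − 0.3078)/0.7070 = 0.553.
- Overall: 0.689/3 + 2 × 0.553/3 = 0.598.
- 222 × 0.598 = 132.8 events (stated 132), and 132/0.598 = 221 patients (stated 222). Then 222/0.95 = 233.7, or 234.
- Power at 132 events is 79.0% by Schoenfeld. The Lachin-Foulkes formula with null variance pooled gives N = 220 and 131.5 events for 80%.

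The stated figures are correct for an 18 + 12 month trial.

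**Step 2: does the event requirement depend on R?** Lachin-Foulkes gives 131.5 events at R = 18 and 132.6 at R = 36. It hardly does.

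**Step 3: the three-year trial (R = 36, F = 12, other inputs unchanged).**
- Placebo: 1 − (0.5000 − 0.0625)/2.0794 = 0.790.
- Experimental: 1 − (0.6242 − 0.1518)/1.4140 = 0.666.
- Overall: 0.707.

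| | 18 + 12 months | 36 + 12 months |
|---|---|---|
| Overall P(event) | 0.598 | 0.707 |
| Events from 222 (power) | 133 (79%) | 157 (84.0%) |
| Events from 234 (power) | 140 (81%) | 165 (85.5%) |
| Patients for 132 events | 221 | 187 (187/0.95 ≈ 197 with dropout) |

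The 132nd event is expected when P(event) reaches 132/222 = 0.595 or 132/234 = 0.564. This is at month 40.6 or month 39.0, against an earliest final analysis at 36 + 12 = month 48.

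**Step 4: sensitivity to accrual shape (assumed patterns, 222 patients, analysis at month 48).**
- Linear ramp over 12 months, then steady: about 150 events, 83% power.
- Linear ramp over 18 months, then steady: about 147 events, 82%.
- Rate rising linearly for all 36 months: about 141 events, 81%.

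**Step 5: sensitivity to the primary population.** If 20% of the 234 fell outside it (an assumption; the article gives no figure), 0.8 × 234 = 187 patients remain. With uniform accrual, 187.2 × 0.707 = 132 events, 79% power.

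**The case against.** The strongest reply is that nothing is miscalculated. The figures reproduce on their stated inputs, the 132-event requirement carries over to a three-year trial, and the discrepancy runs in the safe direction. That all stands, and it limits the point to an unreconciled design assumption. It does not remove it: the article says 222 patients are needed for 132 events, and for the recruitment period it gives elsewhere that is not so.

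A second reply is that 157 events and 84% power depend on uniform accrual and ignore the two-cycle restriction. This also stands; steps 4 and 5 show how far the figures move, and no single replacement number should be inserted without its assumptions.

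A third is that 12 months after closure is worded as a minimum, so an event condition is not excluded and may be set in the full protocol. That is fair, and I do not claim that none exists. But the article presents 132 events as required and then dates the analysis without them, and one sentence would connect the two.

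A reader might also infer that the 40-patient feasibility review faces two conflicting rates, 234/18 = 13 a month and 234/36 = 6.5 a month, and that the Data Monitoring Committee could judge a trial on its three-year plan to be failing. The documents do not support this. The review is to confirm "achievability of planned target recruitment", but Trial design says that it has no formal criteria, and Interim analysis refers to the target of 234 patients. Neither rate is stated as a benchmark.

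**Conclusion.** The point holds as an internal inconsistency with a measurable consequence. Under the article's exponential assumptions, a three-year trial analysed 12 months after closure would have about 157 events from 222 patients (84% power) with uniform accrual, or about 141 to 150 (81 to 83%) with the ramp-up patterns tried, against the stated 132 and 80%. With uniform accrual, 132 events would need about 187 patients (197 with dropout), 16% fewer than 222, and would be reached around month 39 to 41.

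Two stronger readings should be resisted. The first is that the trial is underpowered: the discrepancy adds events. Exclusions from the primary population could use up that margin, as the 20% example shows, but they are a separate matter from the recruitment period. The second is that the 132-event requirement is itself wrong: it is not.

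The contradiction is certain. The magnitudes rest on the accrual pattern, on analysis exactly at month 48, and on the share of patients who enter the primary analysis. The correction is worth making, but it does not threaten the validity of the trial.

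**What to change.** - **Sample size:** restate the calculation for 36 months of accrual plus 12 months, keeping N at 234 and the requirement of 132 events. Give expected events and power at the final analysis as a range, and state the accrual pattern and the primary population assumed. If 18 months is the real plan, correct Patient recruitment and Trial status instead.
- **Outcome analyses:** add a sentence on how the final analysis date relates to the 132 required events. A rule that takes the later of 132 events and 12 months after closure would, under uniform accrual with all patients counted, leave the analysis at month 48. Its value is as protection if events in the primary population come more slowly.

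The cost is protocol and analysis-plan text only. The target of 234 does not change, and no feasibility benchmark needs to be added.

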#### Interim analysis

An interim analysis will occur at the end of the feasibility study with 40 patients and every six months thereafter and results reported to the DMC. Interim data from the feasibility study (numbers of participating centres and monthly recruitment rates) will also be presented to the DMC to evaluate recruitment feasibility of the 234 target. In addition, treatment compliance, AE incidence, and HRQoL data will be reviewed to evaluate if the intervention is safe and acceptable. Later interim analyses will focus on efficacy outcome measures as well as safety. In particular, the DMC will advise on whether the emerging data warrant the potential expansion into a phase III trial. Should the DMC make this recommendation then further funding would be required.

#### Outcome analyses

Overall survival time will be analysed using the Kaplan-Meier method to estimate and plot the survivor functions for each treatment arm, together with summary statistics of median and 12-month survival rates. In addition, 6-month and where available 24-month survival rates will be reported. The difference between treatment arms will be estimated using a hazard ratio generated from a Cox regression model. All estimates will be reported with one-sided 90% confidence intervals. The null hypothesis of no difference between the treatment arms in terms of overall survival time will be tested using the Cox regression model. The primary analysis will be on all patients who have received at least two cycles of protocol treatment.

Progression-free survival time will be analysed in the same way as OS. Measures of HRQoL will be reported on each treatment arm as means over time with 95% confidence intervals. The incidence of adverse events will be reported in the case report form (CRF) and patient diaries on each arm and compared descriptively.

Final analysis of the completed phase II trial will occur once all participants have been recruited and followed up for at least 12 months from closure of the trial to recruitment.

The treatment effect will be evaluated for subgroups of patients defined by age (≤ 70 vs. > 70 years), performance status (Karnofsky Performance Status 60–79 vs. 80–100), sex (male vs. female), symptomatic vs. asymptomatic at baseline, numbers of sprays per day and re-resection group.

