### Dose modifications

TMZ dose modifications, delays, or discontinuation should be made in response to toxicities according to the institution’s usual practice. Amended doses and reasons for any modifications will be recorded at each cycle. Suggested guidance for modifications is provided in Appendix 5. If TMZ cycles are delayed due to TMZ related toxicities, then nabiximols/placebo can be continued during the delay if deemed appropriate by the treating clinician. Any patient with two prior dose reductions who experiences toxicity that would require a third dose reduction of TMZ or a delay of > 2 weeks will have their TMZ, and nabiximols/placebo discontinued and be withdrawn from the trial.

If a toxicity suspected to be related to nabiximols/placebo occurs, then dosing can be suspended or amended until the event has resolved. Patients, whose dose is adjusted, may restart the titration at an appropriate dose and return to their MTD gradually by increasing the number of sprays by one spray per day (Table 2). If a participant requires > 2 weeks off nabiximols/placebo or reduce their dose to < 3 sprays/day, then the patient should stop nabiximols/placebo permanently. TMZ can be continued, if appropriate, at the discretion of the treating physician as per local standard of care.

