## Discussion

### Choice of trial design

A phase II rather than phase III trial design has been chosen for the ARISTOCRAT trial, as the preliminary data on potential efficacy is still sparse. In addition, the feasibility of undertaking such a trial in terms of safety, compliance, and achievability of recruitment needs to be evaluated before embarking on a phase III and this will be done within the early stages of this trial. The choice for the design to be a randomised, double-blind, placebo-controlled trial will ensure an unbiased robust evaluation of the treatment and will allow potential recruitment expansion into a phase III trial should the emerging phase II results warrant this development. In this case, the phase II sample size is synergistic with the requirements for the first stage of a two-arm two-stage phase III trial design.

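### The primary survival analysis keeps only patients who received at least two cycles, so the groups compared are not the randomised groups, although survival is counted from randomisation

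*Protocol article*

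**What the plan says.** The Outcome measures section fixes the endpoint and its time origin: "The primary outcome is OS defined as the time in whole days from the date of randomisation to the date of death from any cause". The Outcome analyses section then fixes the population: "The primary analysis will be on all patients who have received at least two cycles of protocol treatment". It adds "Progression-free survival time will be analysed in the same way as OS", so the restriction reaches PFS too. No analysis of all randomised patients is described anywhere in the article.

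Two further rules act on the analysed population after randomisation. Under Interventions, patients who do not establish their individual spray dose within 14 days are classed as not evaluable and replaced. Under Treatment compliance, patients with a positive urine cannabinoid test may be treated as unevaluable.

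The Sample size section says "the trial requires 132 events to have 80% power (i.e., β = 0.2) to detect a difference with a hazard ratio of 0.68". These events come from 222 patients, and "a further 5% to cover potential dropouts has been added to give a target sample size of 234". The Discussion (Choice of trial design) says that the randomised, double-blind design "will ensure an unbiased robust evaluation of the treatment".

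**The concern.** Whether a patient receives two cycles is known only after randomisation. It depends on surviving, on not progressing (TMZ stops at progression) and on tolerating treatment. The spray is titrated in the first 14 days, so any intolerance specific to it would show inside this window. Blinding does not prevent exclusions caused by a drug's own effects.

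Two things are at stake. First, every retained patient carries guaranteed survival time, because the clock starts at randomisation and entry comes later. Survival curves, medians and 12-month survival are then too high in both arms. The Outcome measures section singles out 12-month survival as clinically relevant, and the Trial delivery section suggests using the control-arm data as a backbone for future trials, so the inflation could carry forward. Second, the between-arm test is no longer protected by randomisation, in a trial whose result is meant to inform expansion to phase III.

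**Working it through.** **Inputs.** From Sample size: placebo median 12 months, so λ₀ = ln 2/12 = 0.0578 per month; HR 0.68, so λ₁ = 0.0394 and median 17.6 months; 2:1 allocation; one-sided α 0.10; 18 months' accrual and 12 months' follow-up; 222 patients, 234 with the allowance. From Interventions: 28-day cycles. From the notes to Table 3: up to 28 days from randomisation to start of treatment. From Patient recruitment and Trial status: three years' recruitment.

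**1. Reproducing the plan's figure.** The Lachin–Foulkes method gives 131.5 events and 219.9 patients, against the stated 132 and 222. Schoenfeld's formula gives (1.2816 + 0.8416)² / [(1/3)(2/3)(ln 0.68)²] = 136.4, and 79% power at 132 events. With P(death) = 1 − [exp(−λF) − exp(−λ(A+F))]/(λA), A = 18 and F = 12, expected deaths are 74 × 0.689 + 148 × 0.553 = 51.0 + 81.8 = 132.8. The plan's figures therefore hold for all randomised patients counted from entry.

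**2. Deaths before a patient can qualify.** The article does not say whether a cycle must be started or completed, so three cuts are shown: day 28 (cycle 2 started), day 56 (two cycles completed) and day 84 (two completed after a 28-day start delay). P(death by t) = 1 − exp(−λt), with day 56 = 1.84 months.

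| Cut | Placebo | Nabiximols | Overall (2:1) | Deaths lost of 222 |
|---|---|---|---|---|
| Day 28 | 5.2% | 3.5% | 4.1% | 9.1 |
| Day 56 | 10.1% | 7.0% | 8.0% | 17.8 |
| Day 84 | 14.7% | 10.3% | 11.8% | 26.1 |

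From day 56 on, deaths alone exceed the 5% allowance.

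**3. Inflation at day 56.** Conditional 12-month survival is 0.500/0.899 = 55.6% on placebo and 0.624/0.930 = 67.1% on nabiximols. Medians become 12.0 + 1.84 = 13.8 and 17.6 + 1.84 = 19.5 months.

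**4. Power (Schoenfeld), removing early deaths only.**

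| Accrual + follow-up | Patients | Deaths, all randomised | Left at day 56 | Left at day 84 |
|---|---|---|---|---|
| 18 + 12 months | 222 | 132.8 (79%) | 115.0 (75%) | 106.7 (72%) |
| 18 + 12 months | 234 | 139.9 (81%) | 121.2 (76%) | 112.4 (74%) |
| 36 + 12 months | 234 | 165.5 (85%) | 146.7 (82%) | 138.0 (80%) |

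**5. Effect on the hazard ratio.** If the only exclusions are deaths before a fixed day, the risk sets after that day are the same as in the full analysis, so under these hazards the hazard ratio is unchanged. Simulation at day 56 (8,000 runs, 222 patients) agrees: at a true HR of 1 the type I error is about 10% with or without the exclusion.

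**6. Arm-dependent, prognosis-related exclusion.** The documents give no rates, so these are assumed scenarios at a true HR of 1, with more exclusion on nabiximols.
- Model A: 234 patients, log-hazard SD 0.5, correlation of prognosis with exclusion 0.5–0.7. Excluding 10% of nabiximols against 5% of placebo gives a type I error of about 12–13%; 15% against 5% gives about 14–17%, with a mean HR near 0.95.
- Model B: 222 patients, stopping confined to a poor-prognosis quarter, deaths before day 56 also removed. Excluding 10%, 15% or 20% of nabiximols against 5% of placebo gives about 16%, 21% or 29%, with a mean HR of about 0.95, 0.90 or 0.86.
- The all-randomised analysis stays at about 10%. If placebo lost more poor-prognosis patients, the bias would run the other way.

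**The case against.** The strongest reply is that the harm to the test is not shown. Three parts of it stand.

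- **Hazard ratio.** A reader might infer that dropping early deaths by itself makes the hazard ratio wrong. Under the plan's hazards it does not (step 5).
- **Differential exclusion.** The Background reports no difference in treatment-emergent adverse events between arms in the phase I trial, and the Abstract speaks of few additional side effects. The Dose modifications section lets TMZ continue after the spray stops, so if cycles are counted by TMZ, spray intolerance need not exclude anyone. However, that trial had 21 patients and used dose-dense TMZ, so it cannot rule out a difference.
- **Power.** A reader might infer that the trial is left underpowered. That follows only from the 18-month accrual in the Sample size section. With 234 patients and three years' recruitment, early deaths alone leave more than 132 events even at day 84.

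Two further limits apply. For PFS, the first scheduled on-treatment MRI is at week 10, after two cycles for a patient on schedule, so scheduled imaging would rarely document progression early enough to be dropped; clinical or unscheduled progression and early death would be. Also, the rule under which some patients "will have their TMZ, and nabiximols/placebo discontinued and be withdrawn from the trial" for repeated TMZ toxicity mostly concerns patients already past two cycles, so it adds little here.

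An unseen analysis plan is no answer, because the article itself names the primary population.

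**Conclusion.** The concern holds for the population rule, and since it affects the primary analysis of the primary endpoint it should be corrected. As written, the analysed groups are selected by events after randomisation, so the unbiased comparison that the article promises is not guaranteed.

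The inflation of the survival estimates follows from the plan's own hazards: at day 56, about 5 to 6 percentage points in 12-month survival and about 1.8 months in each median. It is smaller at day 28 and larger at day 84. Bias in the hazard ratio is possible but not quantified by the documents. It needs failure to reach two cycles to differ by arm and to relate to prognosis, and the type I error figures illustrate assumed rates only. The loss of power is conditional on 18-month accrual and should not be presented as a general consequence; exclusions for toxicity, progression or withdrawal would come on top of the deaths counted here.

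**What to change.** Make the primary analysis of OS and PFS all randomised patients in their allocated arm, followed for death regardless of treatment received. Keep the two-cycle set as a labelled supportive analysis, with receipt of a cycle defined and time preferably counted from a landmark.

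Reconcile the not-evaluable-and-replaced rule under Interventions and the unevaluable rule under Treatment compliance with that population, so that these patients stay in the primary analysis.

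As a separate, minor point, reconcile the withdrawal wording under Dose modifications with the follow-up to at least 52 weeks or death stated under Interventions. The clinical stopping rule itself is not in question.

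The cost is wording only, and no extra patients are needed on account of this change. The population then matches the one from which the 132 events were derived. A small downside is that the estimated effect may be diluted by patients who took little drug.
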